### Participants

All patients will be recruited by 1 single surgeon embedded in a multidisciplinary scoliosis team in the Amsterdam UMC in the Netherlands. Both patients and patients’ legal guardians must sign an informed consent form before the patient is included in the study. The inclusion criteria are (1) a diagnosis of AIS, (2) an age of >7 years, (3) a primary Cobb of >30°, (4) failed nonoperative treatment, (5) a Risser grade of ≤2 and a skeletal age of hand and wrist x-rays of ≤14 years, (6) a nonrigid curve, (7) all Lenke types, and (8) no previous spinal surgery.

A patient who meets any of the following criteria will be excluded from participation in this study: (1) nonidiopathic scoliosis: musculoskeletal or neurologic conditions responsible for the cause of the spine curvature (ie, neuromuscular, congenital, or syndromic scoliosis); (2) history of previous spine surgery; (3) Risser grade >2; (3) disease or deformity likely to affect the stability of the device (ie, inadequate anatomy of pedicles, trauma or tumor in fixation region, severe osteoporosis, bone destruction, or poor bone quality); (4) nonreducible scoliosis; (5) known allergy or intolerance to one of the device material; (6) acute or chronic infections, local or systemic; (7) absence or insufficiency of covering tissues; or (8) pathological obesity.

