### Data Collection and Statistical Analyses

Data will be collected at baseline, directly post surgery, after 2 months, and every 6 months after the operation until 2 years after skeletal maturity (see Table 1).

To describe the included patient group, patient characteristics such as age at surgery, sex, height, weight, medical and surgical history, blood loss during surgery, operative time, length of hospitalization, upper and lower level of fixation, short- and long-term complications (surgical site infections, neurological complications, implant failure, proximal junctional kyphosis, etc), and when applicable, secondary surgery (including the time between the first and second surgery) will be extracted from the patient's medical record. The data will be summarized in tables listing the mean, SD, median, minimum, maximum, and number of subjects for continuous data or in tables listing the quantities and percentages for categorical data, where appropriate.

For the primary goal, to analyze the efficacy of OWSER, the correction of the scoliotic curve will be measured by comparing the preoperative and postoperative Cobb angle with the Cobb angle 2 years after maturity. Radiological parameters will be measured by an orthopedic resident, trained to measure all radiological parameters. Measurements will be randomly verified by a senior experienced spine surgeon. Measured radiological parameters include the main Cobb angle (measured as defined by Cobb [21]), compensatory Cobb angle, correction after surgery, sagittal balance (thoracic kyphosis, lumbar lordosis, and proximal and distal junctional angle), pelvic parameters (pelvic obliquity, sacral slope, pelvic incidence, and pelvic tilt), Risser sign, and vertebral rotation based on full spine standing posterior-anterior and lateral radiographs. Differences between the Cobb angles and growth will be analyzed using repeated ANOVA measures. To correct for possible confounders, a mixed-model regression analysis will be performed including age at surgery, Risser sign, weight, and sex.

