Patient satisfaction and function will be assessed using patient appearance (shoulder imbalance and pelvic imbalance) and patient-reported outcome measurements using the Scoliosis Research Society's-22r (SRS-22r) questionnaire. This questionnaire is provided in Dutch and the use of the questionnaire has previously been validated [22]. The safety of the surgical device will be monitored and registered based on (serious) adverse events and complication rates. Radiological and patient-related outcomes will be used to assess the clinical outcomes and with this, the efficiency of the implant. These parameters will be measured at every follow-up moment (Table 1).

In case of missing values at the follow-up, the patient will remain included in the study. Based on the amount of missing values, the patients will be excluded from the calculations from the specific follow-up moment. This will be described in the results section of the specific study. A *P* value of <.05 will be regarded as statistically significant.

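### The rule for excluding patients with missing values has no threshold and is settled at reporting, and the repeated-measures ANOVA it feeds discards incomplete patients; the mixed model already planned should be primary.

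*Protocol article*

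**What the plan says.** All of this stands in the protocol article, Data Collection and Statistical Analyses, unless noted.

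- **Primary comparison.** Efficacy is judged by "comparing the preoperative and postoperative Cobb angle with the Cobb angle 2 years after maturity". That makes three milestones.
- **Test.** "Differences between the Cobb angles and growth will be analyzed using repeated ANOVA measures".
- **Second model.** "To correct for possible confounders, a mixed-model regression analysis will be performed including age at surgery, Risser sign, weight, and sex". Its stated purpose is confounding, not incomplete data.
- **Missing data.** "In case of missing values at the follow-up, the patient will remain included in the study", followed by "Based on the amount of missing values, the patients will be excluded from the calculations from the specific follow-up moment" and "This will be described in the results section of the specific study".
- **Sample size** (Sample Size section). Correlation 0.5, effect size 0.4, power 80% and significance level 0.05 give 12 patients. A 20% allowance for loss brings the number to 14. The SDs used are 31 before and 11.75 after surgery.

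**The concern.** The rule makes exclusion depend on how much is missing, but gives no quantity, no unit (items, films or visits) and no time at which the decision is fixed. Because it points to the results report, exclusions can be decided with the Cobb angles in view. In a single-arm study of 14 patients with no control group, that discretion acts directly on the primary result.

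The rule also fits the named test poorly. It speaks of leaving a patient out at one follow-up moment while keeping the patient in the study. A classical repeated-measures ANOVA needs a full row per patient, so anyone without the final film also loses their preoperative and postoperative angles from the comparison. What remains is a completer analysis.

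Two things are at stake: a modest loss of power, and a possible selection effect if those without a final film differ from the rest. Selection is plausible here. The final film comes long after surgery, and the article itself anticipates secondary surgery and implant complications. It is a risk, not something the documents show.

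**Working it through.** **1. The plan's own figure.** For one group measured m times, the noncentrality is λ = f²·N·m/(1−ρ), with m−1 and (N−1)(m−1) degrees of freedom. Inputs from Sample Size: f = 0.4, ρ = 0.5, α = 0.05. The article does not state m, so several values were tried.

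| m | smallest N for 80% power |
|---|---|
| 2 | 15 |
| 3 | 12 |
| 4 | 10 |
| 5 | 9 |
| 6 | 8 |

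Only m = 3 gives the stated 12. There λ = 0.16·12·3/0.5 = 11.52, on 2 and 22 degrees of freedom, and power is 0.816. This agrees with an ANOVA on the three milestones.

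**2. What the planned loss leaves.** 12·1.2 = 14.4, stated as 14. Then 14·0.8 = 11.2 complete patients. Power at m = 3:

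| N | λ | power |
|---|---|---|
| 14 | 13.44 | 0.88 |
| 12 | 11.52 | 0.82 |
| 11 | 10.56 | 0.77 |
| 10 | 9.60 | 0.72 |

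**3. Bias among completers.** Simulation with no true change over time, SD 11.75 at all three points, correlation 0.5, and only the final film liable to be missing. The missingness model is an assumption: the log-odds of a missing final film rise by 1.0 or 1.5 per SD of the angle named in the first column, with 21% to 22% lost overall. The likelihood estimate predicts the missing final angles from the two earlier ones. The true value is 0 throughout.

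| Loss depends on | slope | completers, final − postoperative | completers, final − preoperative | likelihood, final − postoperative |
|---|---|---|---|---|
| observed postoperative angle | 1.0 | +1.1° | 0.0° | 0.0° |
| observed postoperative angle | 1.5 | +1.5° | 0.0° | 0.0° |
| unseen final angle | 1.0 | −1.1° | −1.1° | −1.5° |
| unseen final angle | 1.5 | −1.4° | −1.4° | −2.1° |

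In the first two rows the bias falls on the postoperative-to-final contrast, which is the one that shows whether correction is kept. In the last two rows neither method is unbiased, and on this contrast the likelihood estimate is the further from zero.

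**4. Does exclusion change the error rate?** Null simulation of the ANOVA with 14 enrolled, 10,000 runs:

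| Setting | all 14 | after 20% random loss |
|---|---|---|
| equal SDs, uncorrected | 0.051 | 0.048 |
| SDs 31/11.75/11.75, uncorrected | 0.072 | 0.074 |
| SDs 31/11.75/11.75, Greenhouse-Geisser | 0.049 | 0.050 |

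The third SD of 11.75 is an assumption. With it, the variances of the pairwise differences are 31² + 11.75² − 2·0.5·31·11.75 = 734.8 for each contrast with the preoperative angle, and 138.1 for postoperative against final. Sphericity needs these to be equal; epsilon is 0.645. The excess over 5% is there with nobody missing and does not grow materially with random loss. With equal SDs and about 22% loss tied to an angle (slope 1.5), the uncorrected rate was about 0.066.

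**The case against.** Four points can fairly be made for the plan.

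- **An analysis plan may settle the details.** That would answer a gap, but the article states a rule and sends the reader to the results report. The rule as written needs changing.
- **Part of the remedy is already there.** Patients stay in the study, tables list the number of subjects, exclusions will be described, and a mixed model is planned. This stands, and it is why the fix is cheap.
- **The loss is small.** If only the final film is at risk, 14 patients leave 13.3 at 5% missing and 12.6 at 10%, both above 12. The shortfall appears only at about the 20% the plan itself allows for. Power is also measured on the plan's effect size of 0.4. On the cited correction of 89 − 35 = 54 degrees, with an SD of the difference of √734.8 = 27.1, seven patients would already give 0.99. So power is the lesser half of this point.
- **A mixed model is no cure-all.** This stands: see the last two rows of the bias table.

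A reader might also infer more than the documents support.

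- **That exclusion makes the error rate wrong.** Random exclusion leaves it near 5%. The rise to about 7% comes from unequal variances, needs an assumed third SD, and goes away with a standard correction that an analysis plan may contain.
- **That unequal visit schedules leave the ANOVA without common time points.** Visits run "every 6 months after the operation until 2 years after skeletal maturity", and entry at "a Risser grade of ≤2 and a skeletal age of hand and wrist x-rays of ≤14 years" together with an age above 7 years means the number of visits will differ by patient. But the primary comparison uses three milestones that every patient shares. Severe attrition would require an ANOVA over all visits, which the article does not specify.
- **That attrition should be counted from 12.** Twelve is the evaluable number after loss; 14 are enrolled.

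**Conclusion.** The point holds in a limited form. The exclusion rule is undefined and discretionary, and joined to a repeated-measures ANOVA it makes the primary result a completer analysis. At the planned 20% loss this leaves about 11 of 14 patients and power near 0.77 in place of 0.82. If the final film is lost in relation to the observed postoperative angle, the postoperative-to-final change is off by about 1 to 1.5 degrees, which an analysis of all observed angles avoids.

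The bias figures rest on an assumed missingness model, equal SDs of 11.75 and a correlation of 0.5. They are small beside the correction the plan expects, and matter mainly for the claim that correction is maintained. The power figures rest on the plan's own inputs with m = 3 inferred. The sphericity issue is secondary and separate from the exclusion rule. This should be changed, but it does not invalidate the study.

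**What to change.** 1. Delete the sentence that excludes patients according to an amount of missing values.
2. Make the planned mixed model the primary analysis. Use all observed Cobb angles of every operated patient, with time as a three-level category (preoperative, postoperative, two years past maturity), a within-patient covariance that allows unequal variances, and small-sample degrees of freedom. Name a simpler covariance as fallback if the model does not converge.
3. Report at each milestone how many patients contribute, and why the others do not.
4. Pre-specify a sensitivity analysis for missing final angles, for example setting them to the preoperative value. The mixed model does not protect against loss that depends on the unseen angle, so this step is not optional.
5. If the ANOVA is kept in any role, state a sphericity correction such as Greenhouse-Geisser.

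The cost is a wording change: no new data, visits or patients. The one drawback is that an unequal-variance covariance may be hard to fit with 14 patients, hence the named fallback.

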### Adverse Events

Adverse events (AEs) and serious adverse events (SAEs) are documented according to the definition of the Dutch Ethics Committee and will be acted on accordingly. AEs are defined as any undesirable experience occurring to a subject during the study, whether or not considered related to the investigational product. These will be actively reported by the subject or observed by the investigator or his staff. All AEs will be recorded throughout the study, and their severity and relation to the investigational device will be determined.

SAEs are documented as any untoward medical occurrences or effects that result in death, are life-threatening (at the time of the event), require hospitalization or the prolongation of existing inpatients’ hospitalization, in persistent or significant disability or incapacity, are congenital anomalies or birth defects, or involve any other important medical events that did not result in any of the outcomes listed above due to medical or surgical interventions but that could have been based upon appropriate judgment by the investigator.

The research and treatment team must report any SAEs via telephone or email correspondence within 24 hours after the occurrence of the event to the principal investigator and the delegated medical board of directors. A completed initial SAE report must be sent, as indicated in the study’s case report form.

### Data Management

All data will be handled confidentially according to the General Data Protection Regulation (GDPR) guidelines. Research subjects will receive a 3-digit ID number upon beginning the study. One patient identification log (Castor electronic data capture will be maintained separately to identify the research subjects and will only be accessible to the principal investigator and the project leader.

### Sample Size

To perform a sample size analysis, we compared our study to the study conducted by Miladi et al [23]. The sample size calculation is based on an ANOVA analysis and calculated using the statistical program G*Power (Heinrich-Heine-Universität Düsseldorf) [24,25].

Miladi et al [23] reported the results from the precursor of our OWSER system from the higher thoracic spine to the pelvis in 100 patients with NMS. The mean Cobb angle improved from 89° (range, 25°-149°) to 35° (range, 6°-53°) 3 years after surgery [23]. No SDs were reported. In light of this study, we expect a Cobb angle of 35° at maturity. To use these numbers for the sample size calculation, we assumed a normal distribution of the data; as such, the SDs of the preoperative Cobb angle were 31 and 11.75 for the postoperative Cobb angle [26]. We assumed a correlation of 0.5 and an effect size of 0.4 based on the correction described by Miladi et al [23]. The sample size calculation indicated that 12 patients ought to be included to examine the significant difference between the preoperative Cobb angle and the Cobb angle at the latest follow-up (power: 80%, significance level: 0.05).

Additionally, 20% more patients were included to account for a possible loss of subjects in the follow-up. In conclusion, the highest sample size indicated was 12; therefore, the minimal sample size needed for this study to address the primary goal is 14 patients. After the inclusion is completed, a post hoc power analysis will be performed to conclude if a significant number of patients is included in the study.

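### The 80% power stated for 12 patients does not fit the two-measurement comparison it is attached to: at the plan's own effect size of 0.4 that comparison has 71% power, and 0.4 itself does not follow from the plan's means and SDs

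*Protocol article*

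**What the plan says.** The protocol article, Sample Size, says that "The sample size calculation is based on an ANOVA analysis and calculated using the statistical program G*Power". On the inputs it says: "We assumed a correlation of 0.5 and an effect size of 0.4 based on the correction described" in a published series of 100 patients with neuromuscular scoliosis. From that series it takes mean Cobb angles of 89° before surgery and 35° at 3 years. It derives SDs of 31 and 11.75 and expects 35° at maturity. It then states that "12 patients ought to be included to examine the significant difference between the preoperative Cobb angle and the Cobb angle at the latest follow-up". The number is said to hold for a power of 80% and an alpha of 0.05. After an allowance of 20% for loss to follow-up, the target is 14.

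Under Data Collection and Statistical Analyses, the primary goal names three Cobb measurements. Correction is to be "measured by comparing the preoperative and postoperative Cobb angle with the Cobb angle 2 years after maturity". The test is also given there: "Differences between the Cobb angles and growth will be analyzed using repeated ANOVA measures".

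The article does not say how many measurements were entered in the power program.

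**The concern.** The test, effect size, correlation, alpha, power, resulting number and comparison are all stated, so they can be checked against each other. The comparison named is preoperative against one later time point. With two measurements, a repeated-measures ANOVA is the same test as a two-sided paired t test, and the stated inputs do not give 12 for it.

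The overall test across three time points asks a different question: whether the mean Cobb angle differs anywhere among the three. It can be significant because of the immediate postoperative change alone. It does not by itself show that the angle 2 years after maturity differs from the preoperative angle. If the 80% belongs to that overall test, the only power figure in the article describes a hypothesis other than the one in its sentence, and a reader would take the before-to-final comparison to be better supported than the stated inputs allow.

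**Working it through.** **Inputs, all from Sample Size:** effect size 0.4, read as Cohen's f because the calculation is an ANOVA; correlation ρ = 0.5; α = 0.05. Sidedness is not stated, but an ANOVA F test is non-directional. The within-factors routine for one group, with sphericity, is assumed because repeated-measures ANOVA is the planned analysis.

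**Formula.** For n patients and m measurements, λ = n·m·f²/(1 − ρ), with m − 1 and (n − 1)(m − 1) degrees of freedom. Power is the probability that a noncentral F with parameter λ exceeds the 5% critical value.

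**Step 1: reproduce the 12 (m = 3).**
- n = 12: λ = 12 × 3 × 0.16/0.5 = 11.52; df 2 and 22; power 81.6%.
- n = 11: λ = 10.56; df 2 and 20; power 77.4%.

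So 12 is the smallest n reaching 80% with three measurements. With four measurements the answer is 10.

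**Step 2: the comparison named (m = 2).**

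| n | λ = n × 2 × 0.16/0.5 | df | Power |
|---|---|---|---|
| 11 | 7.04 | 1, 10 | 66.8% |
| 12 | 7.68 | 1, 11 | 71.4% |
| 14 | 8.96 | 1, 13 | 79.0% |
| 15 | 9.60 | 1, 14 | 82.1% |

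The required number is 15. As a cross-check, with equal SDs the standardised change is dz = 2f/√(2(1 − ρ)) = 0.8/1 = 0.8. A two-sided paired t test at dz = 0.8 gives the same powers. The row for 11 is roughly what remains of 14 after a 20% loss (14 × 0.8 = 11.2).

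**Step 3: other readings at m = 2.** Dropping the correlation term gives 27. The alternative (SPSS-type or Cohen-type) effect-size conventions give 52. A one-sided paired t test at dz = 0.8 does give 12 (82.9%), but no one-sided test is stated and an ANOVA is not one.

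**Step 4: does 0.4 follow from the stated means and SDs?**
- Mean change: 89 − 35 = 54°.
- SD of change at ρ = 0.5: √(31² + 11.75² − 2 × 0.5 × 31 × 11.75) = √(961 + 138.06 − 364.25) = √734.81 = 27.1°.
- dz = 54/27.1 = 1.99. Power at n = 12 is above 99.9%, and 5 patients would reach 80%.
- On the f scale with the pooled SD: 27/√((961 + 138.06)/2) = 27/23.4 = 1.15, not 0.4.
- Conversely, dz = 0.8 corresponds to 0.8 × 27.1 = about 22°, against the 54° described.

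**Step 5: detectable change.** At n = 12, two-sided α = 0.05 and 80% power, the smallest detectable change is 0.89 SD of change, or 0.89 × 27.1 = about 24° at the implied SD.

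**The case against.** The strongest reply is that the 71% depends entirely on f = 0.4. A reader might infer from Step 2 that 12 or 14 patients are too few to show the correction the plan expects. The documents do not support that: on the plan's own means and SDs the before-to-final comparison has power above 99.9% at 12. This objection stands, and it limits the point to a mismatch between the stated inputs, the stated comparison and the stated result.

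It can also be said that the fault is one of labelling. The primary goal has three measurements, repeated-measures ANOVA is planned, and 12 is exactly right for that test. This is plausible, and no error in the power program's output is alleged. But that three measurements were entered is an inference from the exact match and from the primary goal. The sentence as written still attaches 12 and 80% to a two-measurement difference, and that mismatch does not depend on the inference.

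A reader might go further and argue that power for the lasting difference could collapse if correction is lost after surgery. The plan gives no basis for such scenarios: it expects 35° at maturity, the same value as in the cited series at 3 years. If f = 0.4 is spread over three time points with the correction fully kept, power for preoperative against final at n = 12 is 76%, not far below target.

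Finally, the difference between latest follow-up and 2 years after maturity is a matter of wording. Follow-up is scheduled until 2 years after skeletal maturity, so the two coincide for patients who complete it and differ only for those lost earlier.

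**Conclusion.** The point holds in a conditional form. At f = 0.4, correlation 0.5 and two-sided α = 0.05, preoperative against final Cobb angle has 71% power with 12 patients and 79% with 14, and needs 15 to reach 80%. The stated 12 with 80% fits an overall test over three time points (81.6%). The gap is 3 patients, or about 9 percentage points against the stated 80%. This rests on reading 0.4 as Cohen's f and on a non-directional test; both follow from the stated ANOVA.

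The same section contains a second inconsistency: 0.4 is said to be based on a correction that, with the section's own means, SDs and correlation, gives dz of about 2. The 71% should therefore not be read as evidence that the trial is underpowered for a 54° change. What is wrong is the power statement and its effect size; the recruitment target is not shown to be too small.

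**What to change.** In Sample Size:

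1. State the number of measurements entered to obtain 12.
2. If that number was three, restate the result along these lines: *12 evaluable patients give 82% power for the overall repeated-measures test over three time points and 71% for preoperative versus 2 years after maturity, both at f = 0.4; the change detectable with 80% power at n = 12 is 0.89 SD of change.*
3. Either justify f = 0.4 as a deliberately conservative assumption, or reconcile it with the means of 89° and 35° and the SDs of 31 and 11.75.
4. Replace the reference to latest follow-up with 2 years after maturity, to match the primary goal.

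The cost is rewording only. No endpoint, analysis or recruitment target changes and no extra patients are required, though the power reported for the before-to-final comparison at f = 0.4 becomes less favourable.

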**Methods:**

In 14 selected patients with AIS with Lenke 1-6 curves, minimally invasive PSnF surgery with the OWSER system is performed after the failure of conservative treatment (curve progression of >5° within 1 year). The patients are over 7 years of age, with a major Cobb angle of ≥30°, sufficient flexibility, and a Risser stage of ≤2. Patients will be followed over time, according to the standard medical care. Efficacy will be measured using radiological and patient satisfaction assessments and safety will be determined by the amount of perioperative complications.

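### Minor arithmetic error: adding 20% to 12 patients gives 14.4, which should round up to 15, so a minimum of 14 covers only 2 losses (14.3%)

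*Protocol article*

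**What the plan says.** The Sample Size section sets the base number: "The sample size calculation indicated that 12 patients ought to be included", with "power: 80%, significance level: 0.05". The inputs are given as "We assumed a correlation of 0.5 and an effect size of 0.4", and the method as "The sample size calculation is based on an ANOVA analysis and calculated using the statistical program G*Power". The allowance follows: "Additionally, 20% more patients were included to account for a possible loss of subjects in the follow-up". The conclusion drawn from these is "therefore, the minimal sample size needed for this study to address the primary goal is 14 patients". The Abstract carries the same number: "In 14 selected patients with AIS with Lenke 1-6 curves".

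Two statements under Data Collection and Statistical Analyses bear on this. The primary analysis is described as "comparing the preoperative and postoperative Cobb angle with the Cobb angle 2 years after maturity". Patients with missing follow-up values stay in the study but are left out of the calculations for the visit concerned.

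**The concern.** The 14 is presented as a minimum derived from two figures beside it, 12 and 20%, and it does not follow from them unless a fractional requirement is rounded down. Rounding down defeats the purpose of a minimum.

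The allowance matters because the primary comparison needs a Cobb angle 2 years after skeletal maturity. Patients enter at Risser grade 2 or below, so each must be followed through remaining growth and for 2 years beyond it. A patient lost before then has no value at that time point and drops out of that calculation. If losses exceed what 14 can absorb, the primary analysis has fewer patients than the 12 the plan says it needs.

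**Working it through.** **Inputs.** From the Sample Size section: base N = 12, allowance 20%, final N = 14, power 80%, significance level 0.05, effect size 0.4 (taken as Cohen's f), correlation 0.5. The number of repeated measurements is not stated there. I assume m = 3, from the three time points named for the primary analysis (preoperative, postoperative, 2 years after maturity).

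**Step 1: reproduce the plan's 12.** For a within-subject repeated-measures ANOVA the noncentrality parameter is lambda = f² x N x m / (1 - rho), with m - 1 and (N - 1)(m - 1) degrees of freedom.

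- With m = 3: lambda = 0.16 x N x 3 / 0.5 = 0.96 x N.
- At N = 12: lambda = 11.52 on 2 and 22 degrees of freedom, power 81.6%.
- At N = 11: lambda = 10.56 on 2 and 20 degrees of freedom, power 77.35%, below 80%.

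The smallest N reaching 80% is therefore 12, which matches the plan. With the same inputs, m = 2 needs 15 and m = 4 needs 10, so of these only m = 3 reproduces the plan's figure.

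**Step 2: apply the allowance.**

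- As 20% added to the base: 12 x 1.20 = 14.4, rounded up to 15.
- As protection against 20% loss: 12 / (1 - 0.20) = 15 exactly, and 15 x 0.80 = 12.
- What 14 provides: 14/12 - 1 = 16.7% more than the base.

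The stated 14 is 14.4 rounded to the nearest whole number or down.

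**Step 3: what 14 tolerates.**

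- Losses that still leave 12: 14 - 12 = 2, and 2/14 = 14.3%.
- If 20% of 14 were lost: 0.20 x 14 = 2.8, leaving 11.2, so 11 whole patients.

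**Step 4: the cost in power (m = 3).**

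| Evaluable patients | Power |
|---|---|
| 11 | 77.35% |
| 12 | 81.6% |
| 14 | 88.2% |
| 15 | 90.6% |

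Going from 12 to 11 costs about 4 points (81.6 - 77.35 = 4.25) and leaves power 2.65 points below the 80% target.

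**The case against.** **No loss rate is stated.** A reader might infer that the plan forecasts a 20% loss and fails to cover it. The article does not say this: it describes 20% more patients, which is a multiplier on recruitment. This stands, so the figure of 11 evaluable patients is conditional on reading the 20% as a loss rate. The stated purpose of the allowance makes that reading reasonable, and the literal reading also falls short, since 14 is only 16.7% more than 12.

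**Fourteen is traceable.** A reader might infer that no rounding convention yields 14. That is too strong, because 14.4 rounded to the nearest whole number is 14. The fault is using that convention for a minimum.

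**The consequence is small.** This stands. Fourteen is described as a minimum, so enrolling a fifteenth patient would not breach the plan. Moreover, the Cobb figures in the same section imply a much larger effect. With means of 89° and 35°, SDs of 31 and 11.75 and correlation 0.5, the SD of the difference is √(31² + 11.75² - 2 x 0.5 x 31 x 11.75) = 27.1° and the standardised paired difference is 54/27.1 = 1.99. A paired t test would then need only 5 patients. Whether those figures suit this population, or lead to an effect size of 0.4, is a separate question.

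**A larger power deficit might be inferred from a two-measurement comparison.** With m = 2 and the same inputs, power is 66.8% at 11 patients. But it is already 71.4% at 12, before any loss. Most of that gap comes from the number of measurements and cannot be charged to the allowance.

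**Loss need not be total.** A patient with missing visits still contributes elsewhere, and a mixed-model regression is also planned. This softens the point without removing it, because a patient lost before 2 years after maturity still lacks the primary end point.

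**Conclusion.** The point holds as a minor arithmetic error. The stated minimum does not follow from the plan's own 12 and 20%: rounding up, or dividing by 0.80, gives 15. The size is one patient. Fourteen protects the required 12 against at most 2 losses. At 11 evaluable patients power is about 77%, under 3 points below target.

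The rounding result rests only on the article's stated figures. The power figure also assumes three measurements, that the effect size is Cohen's f, and that the 20% is a loss rate. A reader might go further and conclude that the study is inadequately sized for its primary goal. One missing patient does not support that conclusion.

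**What to change.** In the Sample Size section, keep 14 and restate the allowance as 'up to 2 of 14 patients (14%) lost', adding that power would be about 77% with 11 evaluable patients and that this assumes three measurements. This changes one sentence and needs no extra patient. The downside is a slightly less favourable stated allowance.

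If the sponsor prefers to keep the 20%, the minimum becomes 15 in both the Sample Size section and the Abstract, at the cost of one patient. With 5 patients included by October 14, 2023 and inclusion hoped to finish by the beginning of 2025, either correction was still open at the time of the article.
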